**Methods/Design:**

Women with PPROM and persisting oligohydramnios between 16 and 24 weeks gestational age will be asked to participate in a multi-centre randomised controlled trial. Intervention: random allocation to (repeated) abdominal amnioinfusion (intervention) or expectant management (control). The primary outcome is perinatal mortality. Secondary outcomes are lethal pulmonary hypoplasia, non-lethal pulmonary hypoplasia, survival till discharge from NICU, neonatal mortality, chronic lung disease (CLD), number of days ventilatory support, necrotizing enterocolitis (NEC), periventricular leucomalacia (PVL) more than grade I, severe intraventricular hemorrhage (IVH) more than grade II, proven neonatal sepsis, gestational age at delivery, time to delivery, indication for delivery, successful amnioinfusion, placental abruption, cord prolapse, chorioamnionitis, fetal trauma due to puncture. The study will be evaluated according to intention to treat. To show a decrease in perinatal mortality from 70% to 35%, we need to randomise two groups of 28 women (two sided test, β-error 0.2 and α-error 0.05).

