**Discussion:**

This study will answer the question if (repeated) abdominal amnioinfusion after midtrimester PPROM with associated oligohydramnios improves perinatal survival and prevents pulmonary hypoplasia and other neonatal morbidities. Moreover, it will assess the risks associated with this procedure.

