Pregnancies complicated by midtrimester PPROM are associated with high immediate and long-term costs. These are caused by extended maternal hospital admissions, increased incidence of premature delivery, and frequent neonatal complications hereafter requiring NICU-admission.

Amnioinfusion might improve fetal outcome by preventing pulmonary hypoplasia, by preventing neurological complications, increasing time to delivery interval, and improving fetal biophysical profile through prevention of umbilical cord compression. It also might prevent fetal deformity [7]. Porat et al. [8] reviewed serial transabdominal amnioinfusion and meta-analysed observational as wel as randomised studies. The only two included randomised studies however were on women with PPROM between 24 and 34 weeks whereas the critical interval for development of pulmonary hypoplasia, the canalicular phase, exists between 16 and 28 weeks gestation. One quasi-randomised study included women with PPROM before 24 weeks. There were two observational studies on PPROM before 24 weeks. Recently, Roberts et al. [9] published the only randomized trial on PPROM between 16 and 24 weeks. They found no difference in the primary outcome (perinatal mortality 19/28 vs. 19/28; RR 1.0; 95% CI0.70-1.43), maternal or neonatal morbidity. The observed difference in long term outcome (4/28 morbidity free survival at 2 years in the treatment group vs 0/28 in the group with expectant management) justifies further study.

Adverse events after antepartum transabdominal amnioinfusion have been reported. It is not clear which adverse effects are to be attributed to the procedure rather than to the condition of PPROM and oligohydramnios, since conservatively managed PPROM carries high risks inherent to the condition itself [7]. Waters and Mercer recently reviewed perinatal mortality after conservatively managed PPROM <26 weeks [5]. Meta-analysis of 6 studies (n = 275) shows a perinatal mortality of 54%, (if restricted to <24 weeks this incidence is 57%). These data are biased by the fact that patients not amenable to continued expectant management were often excluded (i.e. stillbirths, pregnancy terminations), and therefore survival is likely to be overestimated.

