### Study parameters/endpoints

We will compare two groups:

1) Amnioinfusion for midtrimester PPROM with oligohydramnios, and

2) Expectant management for midtrimester PPROM with oligohydramnios.

The primary outcome measure will be perinatal mortality, defined as intrauterine death, intrapartum death or neonatal death in the first 28 days of life.

Secondary outcomes are:

• Gestational age at delivery.

• Time from membrane rupture to delivery.

• Indication for delivery.

• Successful amnioinfusion (defined as retention of infused fluid as defined by a single deepest pocket of amniotic fluid of more than 2 cm for at least 48 hours).

• Placental abruption.

• Cord prolapse.

• Chorioamnionitis, (defined as fever before or during labour as a temperature greater than 37.5°C on two occasion more than one hour apart or a temperature > 38.0°C with either uterine tenderness (or contractions), leucocytosis, maternal or fetal tachycardia, or a foul-smelling vaginal discharge in absence of any other cause of hyperpyrexia).

• Fetal trauma due to puncture.

• Maternal length of stay in hospital.

Occurrence of secondary outcomes placental abruption, cord prolapse, chorioamnionitis and fetal trauma will be related to the number of amnioinfusions that have been performed.

Neonatal endpoints:

• Lethal pulmonary hypoplasia diagnosed according to radiological, clinical and pathological criteria. Pathological criteria are based on radial alveolar counts and lung/body weight ratios according to Askenazi and Perlman [11], when radial alveolar counts cannot be obtained, criteria by Wigglesworth et al. will be used [12]. Clinical criteria used to diagnose lethal pulmonary hypoplasia are: immediate onset of severe respiratory insufficiency after birth, small lung capacity and requirement of high ventilatory pressures in the absence of obstruction or atelectasis. Radiological criteria according to Leonidas will be used [13].

• Non-lethal pulmonary hypoplasia diagnosed using same clinical and radiological criteria in surviving neonates.

• Survival till discharge from NICU.

• Neonatal mortality, defined as neonatal death in the first 28 days of life.

• Chronic lung disease (CLD), CLD defined as oxygen dependency at 28 days of life [14].

• Number of days on ventilatory support.

• Length of stay in hospital.

• Necrotising enterocolitis (NEC) more than stage I and defined according to the criteria of Bell et al. [15].

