### Sample size calculation

A sample size calculation was based on an expected rate of perinatal mortality of 70% with expectant management, to be reduced to 35% with amnioinfusion. Using a two-sided test, with a β-error of 0.20 and an α-error of 0.05 a sample size of 56 women (28 in each arm) is needed.

An interim analysis is planned after the follow up data of the first 28 women that have been included. The analysis will be performed using the O’Brien-Flemming alpha spending function meaning a nominal P value of less than 0.005 will be considered to indicate statistical significance [16]. If there is a significant difference in the primary outcome the trial will be stopped.

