### Statistical analysis

The analysis of the randomised clinical trial will be performed on an intention-to-treat principle. The differences between the amnioinfusion and expectant management will be assessed by calculating the ratio of the outcome rates in the two groups. Hence, the measure of association is a relative risk (RR) with a 95% confidence interval (CI), calculated using a log-binomial model. Time to delivery will be evaluated by Cox proportional hazard analysis, Kaplan-Meier estimates and tested with a log rank test.

In case of equivalence between outcomes, the analysis will be repeated on an “as-treated” basis. Subsequently, primary and secondary outcomes will be described in a subgroup of women with successful amnioinfusion (retention of infused fluid first 48 hours). All analyses will be adjusted for the fact that an interim analysis will be performed using the O’Brien-Flemming alpha spending function [18]. Consequently, a nominal P value of less than 0.049 will be considered to indicate statistical significance.

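### Pulmonary hypoplasia is an outcome only in two pieces split by survival, so neither planned relative risk estimates whether amnioinfusion prevents it

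*Protocol article*

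**What the plan says.** The Discussion part of the abstract states that the trial will answer whether amnioinfusion "improves perinatal survival and prevents pulmonary hypoplasia and other neonatal morbidities". The Background gives the same mechanism: "Amnioinfusion might improve fetal outcome by preventing pulmonary hypoplasia".

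The outcomes are split. The abstract's Methods/Design part reads "Secondary outcomes are lethal pulmonary hypoplasia, non-lethal pulmonary hypoplasia, survival till discharge from NICU, neonatal mortality". Study parameters/endpoints defines the two pieces as "Lethal pulmonary hypoplasia diagnosed according to radiological, clinical and pathological criteria" and "Non-lethal pulmonary hypoplasia diagnosed using same clinical and radiological criteria in surviving neonates". Neither list contains hypoplasia irrespective of survival.

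Statistical analysis says that group differences will be "assessed by calculating the ratio of the outcome rates in the two groups", expressed as a relative risk with a 95% confidence interval. Read with the outcome lists, this gives each of the two hypoplasia outcomes its own relative risk. Nothing there combines them.

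**The concern.** Prevention is a statement about how often hypoplasia occurs. The two listed outcomes are told apart by whether the baby lives, and survival is what the trial sets out to change. An affected baby who is kept alive for any reason moves from the first outcome to the second, although its lungs are no different.

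If fatality among affected babies differs between arms, a fall in lethal hypoplasia could be reported as prevention when occurrence has not changed. A rise in non-lethal hypoplasia could be reported as harm for the same reason. A real reduction in occurrence could also be exaggerated by one ratio and hidden by the other.

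**Working it through.** **The plan's own figure.** The article gives no planning figure for hypoplasia. Its only planning rates are for the primary outcome: "expected rate of perinatal mortality of 70% with expectant management, to be reduced to 35% with amnioinfusion". The unpooled two-proportion formula gives (1.960 + 0.842)² × (0.70×0.30 + 0.35×0.65) / 0.35² = 28.03 per arm, which matches the stated 28 to the nearest whole number. Nothing below depends on it.

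**Inputs.**
- Occurrence *h*: 19% is the Background's review figure for rupture before 24 weeks; its wider range is 1% to 48%.
- Case fatality *c* among affected babies: not given. Assumed 0.70 (expectant) v 0.35 (amnioinfusion), borrowed from the all-pregnancy mortality rates. The alternative is 0.80 v 0.40.
- Pre-neonatal deaths: the Dutch cohort in the Background had 71% perinatal mortality, with 38% of deaths neonatal.

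**Formulas**, with all randomised women as denominator and subscripts 1 for amnioinfusion and 0 for expectant management:
- Lethal rate = *h·c*, so lethal RR = (*h*₁/*h*₀) × (*c*₁/*c*₀).
- Non-lethal rate = *h*(1−*c*), so non-lethal RR = (*h*₁/*h*₀) × (1−*c*₁)/(1−*c*₀).
- Any hypoplasia: RR = *h*₁/*h*₀.

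The first two equal the third only when *c*₁ = *c*₀.

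**Results.**

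| Scenario | Lethal RR | Non-lethal RR | Any RR |
|---|---|---|---|
| Equal *h*; *c* 0.70 v 0.35 | 0.35/0.70 = 0.50 | 0.65/0.30 = 2.17 | 1.00 |
| Equal *h*; *c* 0.80 v 0.40 | 0.40/0.80 = 0.50 | 0.60/0.20 = 3.00 | 1.00 |
| *h* halved; *c* 0.70 v 0.35 | 0.5×0.50 = 0.25 | 0.5×2.17 = 1.08 | 0.50 |
| *h* 40% to 30%; *c* 0.80 v 0.40 | 12%/32% = 0.375 | 18%/8% = 2.25 | 0.75 |

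With equal *h* = 19% and *c* 0.70 v 0.35, lethal is 13.3% v 6.65% and non-lethal 5.7% v 12.35%. That is 3.7 v 1.9 and 1.6 v 3.5 expected cases among 28 women per arm. The sums are 19.0% v 19.0%.

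**Survivors as denominator.** This is no general cure. With equal *h*, overall survival 30% v 65% and assumed *c* 0.90 v 0.45, the non-lethal RR among survivors is (0.55/0.65)/(0.10/0.30) = 2.54. It returns to 1.00 only in the special case where fatality among affected babies equals overall mortality in each arm.

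**Does the simple sum measure occurrence?** Not fully. In the Dutch cohort, 0.71 × (1 − 0.38) = 0.71 × 0.62 = 44% of pregnancies ended in death before the neonatal period. Such babies cannot meet clinical or radiological criteria; only autopsy can classify them, and the Background notes that complete autopsy data were often lacking. As an assumption, let amnioinfusion halve this 44% to 22%, leave the diagnosis rate among live-born babies unchanged, and let no fetal death be classified. Diagnosed hypoplasia over all randomised then has RR 0.78/0.56 = 1.39 with no change in lung growth. The combined outcome therefore needs a rule for these deaths.

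**The case against.** Four points on the other side have force.

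- **The example is assumed.** Case fatality among babies with hypoplasia is not in the article, and applying all-pregnancy mortality to this subgroup is a convenience. A reader might infer that the planned comparisons simply track survival, or that ratios near 0.50 and 2.17 should be expected. The article supports neither. The first is exact only if occurrence is equal between arms; otherwise each ratio mixes both effects. The second rests on the chosen fatality. What stands is the algebra: whenever fatality differs, neither ratio is the occurrence ratio.
- **The total can be recovered.** The two categories do not overlap, so a reader could add the two rows. It would thus be too strong to say that the trial collects nothing on occurrence. But the sum is not prespecified, so relying on it would be a choice made after the results. A baby who meets the criteria but dies of another cause, or before birth, also has no clear place in either category.
- **A power loss might be inferred from the split.** That does not hold up. The 10% for lethal cases comes from one Dutch cohort and the 19% and 48% from two different reviews, so they are not part and whole of one population. At 19%, likelihood-ratio power to detect a halving at 28 per arm is 19%, against 16% at 10%. No version is adequately powered.
- **Fatal and survivable hypoplasia are clinically distinct.** They are, and this is a good reason to keep reporting both. Whether the components are also tested is a matter of preference.

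That a journal article condenses the full protocol does not answer the point. The outcomes are listed in both the abstract and the methods, and both lists fix only the split form.

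**Conclusion.** The point holds as a mismatch between question and outcome. The article promises an answer on prevention of hypoplasia, and no planned comparison estimates its occurrence. The conclusion rests on the outcome definitions and the algebra. It bites to the extent that fatality among affected babies differs between arms, which is plausible in a trial designed to halve mortality but is not quantified in the article. The ratios of 0.50, 2.17 and 1.00 are illustrative only. The weight is low: hypoplasia is a secondary outcome, and the primary comparison and sample size are untouched.

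**What to change.** In the abstract's outcome list and in Study parameters/endpoints, add a prespecified secondary outcome, *any pulmonary hypoplasia (lethal or non-lethal)*, with all randomised women as denominator and the same relative risk. Base any statement about prevention on it.

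State how fetal and intrapartum deaths count: by the autopsy criteria where an autopsy is available, with a stated rule where it is not. Beside it, report *perinatal death or pulmonary hypoplasia*, which does not depend on live birth. This is a check and not a substitute, because mortality dominates it. In the equal-occurrence example at 19%, it is 70% + 5.7% = 75.7% v 35% + 12.35% = 47.35%, a ratio of 0.63 although occurrence is unchanged.

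Keep lethal and non-lethal hypoplasia as reported components.

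The cost is wording and one classification rule, with no new data collection. The downside is that the combined outcome mixes severities and diagnostic bases, since pathology is available only for deaths. That is why the components should stay visible.

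### An effective treatment can appear to increase chronic lung disease (CLD), because the planned relative risk makes no provision for death before day 28

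*Protocol article*

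**What the plan says.** The Aims section of the protocol article puts neonatal morbidity beside perinatal mortality in the primary aim. Under Study parameters/endpoints, the neonatal list includes "Chronic lung disease (CLD), CLD defined as oxygen dependency at 28 days of life" and "Number of days on ventilatory support", together with hospital stay, NEC, PVL, IVH and sepsis. One morbidity, non-lethal pulmonary hypoplasia, is explicitly confined to children who survive. The others have no stated population, and no endpoint combines death with a morbidity.

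The Statistical analysis section sets the intention-to-treat principle and one general comparison, the ratio of outcome rates: "the measure of association is a relative risk (RR) with a 95% confidence interval (CI), calculated using a log-binomial model". Only time to delivery has a method of its own. No rule says how a child who dies enters the comparison of a morbidity.

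The Sample size calculation assumes an "expected rate of perinatal mortality of 70% with expectant management, to be reduced to 35% with amnioinfusion".

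**The concern.** CLD is a status at day 28. The primary outcome counts intrauterine, intrapartum and neonatal deaths over the same 28 days, so the children who can have CLD are exactly those without a primary event. The design expects amnioinfusion to more than double their number. An estimator that ignores this mixes two things: whether treatment changes the risk of CLD, and whether treatment keeps a child alive long enough to be classified.

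Counting over all randomised keeps the randomised comparison but scores a dead child as free of CLD. Counting over survivors removes that error but compares groups that the treatment itself has selected. At stake is the morbidity half of the stated aim: a treatment that saves lives could be reported as raising CLD.

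**Working it through.** **Inputs from the article.** Perinatal mortality is 70% v 35%, so survival to day 28 is 30% v 65%. There are 28 women per arm, and the final nominal significance level is 0.049. In the Dutch cohort described in the Background, 38% of deaths were neonatal.

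**Inputs assumed.** The article gives no CLD risk in survivors, *m*. It is taken as equal in both arms and varied. Ventilation days and the risk in extra survivors are also assumed, as marked below.

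**The plan's own figure.** With the unpooled normal approximation, n = (1.960 + 0.842)² × (0.70×0.30 + 0.35×0.65) / 0.35² = 28.03 per arm, which reproduces the stated 28. The rates below are therefore those the design was built on.

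**Children who can have CLD.** 28 × 0.30 = 8.4 v 28 × 0.65 = 18.2.

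**CLD over all randomised.** The rates are 0.30*m* v 0.65*m*, so the relative risk is 0.65/0.30 = 2.17 for any *m*, with no true effect on CLD. Death or CLD has rate 1 − S(1 − *m*), where S is survival.

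| *m* | CLD, expectant v amnioinfusion | RR | Chance of nominally significant harm | Death or CLD, expectant v amnioinfusion | RR |
|---|---|---|---|---|---|
| 30% | 9.0% v 19.5% | 2.17 | 20.5% | 79.0% v 54.5% | 0.69 |
| 50% | 15.0% v 32.5% | 2.17 | 33.2% | 85.0% v 67.5% | 0.79 |
| 70% | 21.0% v 45.5% | 2.17 | 51.0% | 91.0% v 80.5% | 0.88 |

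The fourth column sums the two binomial distributions (28 per arm) over results with p < 0.049 on a pooled z test, in the direction against amnioinfusion. It approximates the log-binomial analysis. For the all-randomised relative risk to reach 1, CLD risk in survivors would have to be multiplied by 0.30/0.65 = 0.46, a 54% reduction.

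**CLD among survivors.** Let those who would survive under either policy (30% of randomised) have risk m0, and the extra survivors (65% − 30% = 35%) have risk m1. Then RR = (0.30·m0 + 0.35·m1) / (0.65·m0). If m1 = m0, RR = 1.00. With m0 = 30% and m1 = 50%, 70% or 90%, RR = 1.36, 1.72 or 2.08. The split assumes that treatment turns no survivor into a death.

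**Morbidities possible in any liveborn child (NEC, PVL, IVH, sepsis).** If 38% of deaths are neonatal in both arms, fetal or intrapartum deaths are 0.70 × 0.62 = 43.4% v 0.35 × 0.62 = 21.7%. Liveborn children are 56.6% v 78.3%, a ratio of 1.38. That is the inflation over all randomised when every liveborn child has the same risk.

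**Ventilation days.** Assume 10 to 30 days in survivors, 3 in neonatal deaths and 0 in fetal deaths. At 10 days the means over all randomised are 0.30×10 + 0.70×0.38×3 = 3.80 v 0.65×10 + 0.35×0.38×3 = 6.90, a ratio of 1.82. At 30 days the ratio is 2.03. Over liveborn children the ratios are 1.31 to 1.47. All arise with identical ventilation in survivors.

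**The case against.** The strongest objection is that the article names no denominator. Intention to treat fixes the arm in which a woman is counted. It need not place fetal deaths in the denominator for CLD, and one morbidity already has its own population. Denominators and rules for deaths are commonly left to an analysis plan or full protocol, neither of which is shown. Mortality is the primary outcome, and neonatal mortality and survival to NICU discharge are listed too, so a careful reader would see the survival difference.

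Much of this stands. The unstated denominator is not itself the fault, and the 2.17 belongs to one reading only. But the choice of denominator does not settle the matter: over all randomised the measure is distorted by survival, and over survivors it is not a randomised comparison. A remedy needs an outcome that includes death, and the choice of outcomes belongs to the protocol.

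Four stronger readings are tempting and not supported:

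- That amnioinfusion *will* look harmful. Among survivors the relative risk can be 1.00, a fall in CLD risk of more than 54% in survivors would still show as benefit over all randomised, and significant harm is far from certain.
- That ventilation days are to be compared by relative risk. A log-binomial model cannot apply to a count, and the article states no method for them.
- That no child who dies can have any of these outcomes. NEC, PVL, IVH and sepsis can occur in a liveborn child who later dies; only fetal or intrapartum death precludes them.
- That the plan dropped the result it cites as its justification ("4/28 morbidity free survival at 2 years in the treatment group vs 0/28"). That is a two-year outcome, and the article foresees a separate application for follow-up at two and five years.

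**Conclusion.** The point holds in this form: as specified, the CLD comparison can show harm from a treatment that only saves lives. At the design rates the distortion over all randomised is a relative risk of 2.17, given equal CLD risk in survivors. Among survivors it runs from 1.00 to 2.08 under the assumed risks above. Non-lethal pulmonary hypoplasia shares the survivor-only problem: if treatment turned lethal into non-lethal hypoplasia, that endpoint would register harm. Ventilation days are distorted in the same way as CLD, with no method or rule for death stated. NEC, PVL, IVH and sepsis are affected less, by about 1.38 if the 38% share of neonatal deaths applies to both arms, which is an assumption.

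The sizes depend on the planned mortality difference; if mortality were equal in the two arms, the all-randomised inflation would vanish. The primary outcome, sample size and stopping rule are untouched. Severity is moderate.

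**What to change.** - Make death by day 28 or CLD, over all randomised, the comparative secondary outcome in place of CLD alone. At the design rates its relative risk is 0.69 to 0.88 for assumed CLD risks in survivors of 30% to 70%.
- Compare ventilation days with a measure that ranks death worst, for example a rank comparison placing every death below every survivor and ordering survivors by days. This needs only survival status and the total already listed.
- For non-lethal hypoplasia, NEC, PVL, IVH and sepsis, report survival without the morbidity over all randomised, with the protocol's own definitions and a named time point for survival.
- Label survivor-only and liveborn-only figures descriptive, and state their denominators.

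The cost is wording and a few tables from outcomes already collected, settled before results by arm are seen. The drawback is that a composite mixes events of unequal weight. With 70% v 35% mortality, death dominates it, so a benefit on death or CLD would not show that CLD itself was reduced. The components must therefore be shown beside it.

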• Periventricular leukomalacia (PVL) more than grade I and defined according to the classification described by De Vries et al. [16].

• Severe intraventricular hemorrhage (IVH) more than grade II and defined according to the criteria of Papile et al. [17].

• Proven neonatal sepsis defined as (1) Positive blood culture taken at birth or (2) within 72 hours two or more symptoms of infection (apnea, temperature instability, lethargy, feeding, intolerance, respiratory distress, hemodynamic instability) plus one of three items: (a) positive blood culture (culture proven sepsis); (b) CRP > 20 (suspicion sepsis); (c) positive surface cultures of a known virulent pathogen (suspicion sepsis).

The neonatal endpoints will be defined by two neonatologists. The status of these endpoints will be evaluated at six months corrected age. Additional application for long-term follow-up of children (2 and 5 years) and mothers will be performed.

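### The secondary outcome named proven neonatal sepsis also counts cases that its own definition labels as suspicion only

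*Protocol article*

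**What the plan says.** The definition is in the protocol article, Study parameters/endpoints, among the neonatal endpoints. It opens with the name and the two limbs: "Proven neonatal sepsis defined as (1) Positive blood culture taken at birth or (2) within 72 hours two or more symptoms of infection". The second limb is completed by "plus one of three items: (a) positive blood culture (culture proven sepsis", and the other two items follow: "b) CRP > 20 (suspicion sepsis); (c) positive surface cultures of a known virulent pathogen (suspicion sepsis".

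The Abstract (Methods/Design) lists the outcome only under the stricter name, "proven neonatal sepsis". The document lists no suspected-sepsis outcome and does not say that the two kinds of case will be tabulated apart. On adjudication it says "The neonatal endpoints will be defined by two neonatologists", without a rule for cases that meet only a suspicion item. The Statistical analysis section makes the relative risk, from a log-binomial model, the measure of effect.

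**The concern.** The name of the outcome and two of its qualifying criteria contradict each other within one sentence. The connective is one of three, so a suspicion item suffices without any positive blood culture. A reader of the trial report who sees a rate of proven sepsis will take it as culture-confirmed, and under this definition it need not be.

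Two things are at stake. The first is labelling: the report would call proven what the protocol calls suspected. The second is the comparison between arms. If less specific cases arise at a similar rate in both arms, adding them pulls the relative risk for culture-proven sepsis towards 1. The definition is given in full here, so this is not a detail that a condensed article has left to another document.

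**Working it through.** The plan states no sepsis rate, so there is no figure to reproduce. The check is mainly one of logic.

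**1. The rule as written.** Proven = (1) OR [two or more symptoms within 72 hours AND (a OR b OR c)]. This gives four routes:

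| Route | Requirement | Label inside the definition | Counted as proven |
|---|---|---|---|
| 1 | Positive blood culture at birth | none beyond the outcome name | yes |
| 2a | Symptoms + positive blood culture | culture proven | yes |
| 2b | Symptoms + CRP > 20 | suspicion | yes |
| 2c | Symptoms + surface culture of a known virulent pathogen | suspicion | yes |

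Two of the four routes rest on a blood culture. The other two do not, and the definition itself calls them suspicion. A baby who meets only 2b or 2c is still counted as proven.

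**2. Whether another place repairs this.** The Abstract repeats the stricter name. The outcome list has no suspected-sepsis entry. The two neonatologists would be applying this definition. Nothing in the document separates the categories.

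**3. Direction of the effect, as a purely hypothetical illustration.** Let p1 and p0 be the culture-proven rates in the two arms, and let s be an equal extra rate in each arm meeting only 2b or 2c. The pooled relative risk is (p1 + s)/(p0 + s). All values below are assumed; none comes from the document.

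- p1 = 0.20, p0 = 0.10, s = 0: 0.20/0.10 = 2.00
- s = 0.15: 0.35/0.25 = 1.40
- s = 0.30: 0.50/0.40 = 1.25

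The absolute difference stays at 0.10 throughout; it is the ratio, the plan's chosen measure, that shrinks. Because s is the same in both arms, this shows non-differential dilution and nothing else.

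**4. How many babies this could concern.** The sample size is 28 per arm. The Background cites a retrospective analysis from three Dutch centres with 71% perinatal mortality in singletons, 38% of it neonatal, so 62% of deaths fell before or during birth. Assuming that this split applies here:

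- arm at 71% mortality: 28 × (1 − 0.71 × 0.62) = 28 × 0.560 ≈ 16 live births
- arm at the targeted 35%: 28 × (1 − 0.35 × 0.62) = 28 × 0.783 ≈ 22 live births

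At the assumed 10% and 20%, culture-proven cases would number about 16 × 0.10 = 1.6 in one arm and between 16 × 0.20 = 3.2 and 22 × 0.20 = 4.4 in the other. With so few events the trial could not usefully tell a relative risk of 2.0 from 1.25.

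**The case against.** The strongest reply is that the bracketed labels show an intention to keep culture-proven and suspected cases apart; otherwise they have little purpose. The article is condensed, the tabulation may sit in a fuller document, and the paediatricians who assess outcomes are blinded. Part of this stands: separate reporting may have been intended, so misreporting is not certain. It does not remove the contradiction, because the text pools all items under the name proven and nowhere says that they will be split. Blinding protects against biased ascertainment but cannot repair a definition that combines unlike cases.

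A second reply is that the practical effect is small: one of 20 listed secondary outcomes (9 obstetric and maternal, 11 neonatal), with few events. That stands too, and it limits the weight of the point.

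Two stronger readings are tempting, and the document does not support them.

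- Apnea and respiratory distress are on the symptom list, and the Background notes overlapping symptoms among hypoplasia, congenital pneumonia and respiratory distress syndrome. A reader might infer that any effect of amnioinfusion on the lungs passes into the sepsis outcome. Respiratory signs alone never qualify, however: the second limb always needs a blood culture, CRP > 20 or a surface culture as well. The document does not tie those items to lung development, and the equal-rate illustration does not show such a leak.
- A reader might infer that neonatal sepsis should serve as the endpoint for infection harm of the procedure. The Discussion names chorioamnionitis, not neonatal sepsis, among the potential harms. Chorioamnionitis has its own definition, is to be related to the number of infusions, and is a reason for discontinuation under Safety reporting.

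**Conclusion.** The definition contradicts itself and should be corrected. Applied literally, it counts babies with two symptoms and only CRP > 20, or only a positive surface culture, as proven sepsis, although it labels both items as suspicion. This follows from the wording alone and needs no assumption.

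Pooling these cases could dilute a difference in culture-proven sepsis, provided that they occur at similar rates in both arms. The size cannot be derived; the relative risks of 1.40 and 1.25 only illustrate the direction under invented rates. The consequence is confined to the naming and interpretation of one secondary outcome with few expected events. The sample size rests on perinatal mortality and is unaffected, as are the primary analysis and the interim rule.

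**What to change.** Make one of two changes to the outcome definition before the data are analysed.

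- **Split.** Restrict proven sepsis to the blood-culture routes, (1) and (2a), and report babies who meet only (2b) or (2c) as a separate outcome, suspected sepsis.
- **Rename.** If the pooled outcome is kept, call it proven or suspected sepsis wherever it appears, including the Abstract, and show the culture-proven subset beside it.

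Either resolves the contradiction. The split gives the cleaner endpoint at the cost of fewer events under the proven label and a less precise relative risk. Renaming keeps the event count but leaves a less specific headline outcome. The document does not describe the sepsis data fields, but applying the definition already requires knowing which item each baby met, so neither change should need new data collection. It would be enough to confirm that the case report form records the qualifying item, including the blood-culture result.
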